### Recruitment

2.3

Participants will be recruited from inpatient or outpatient settings in Sichuan Provincial People's Hospital. We will also recruit patients through advertise posters or local media. Patients who meet the inclusion criteria will be asked to provide written inform consent, and baseline evaluation including basic information collection, measurement of bone metabolic markers, measurement of serum H_2_S will be performed subsequently.

### Data collection

2.4

#### Basic information

2.4.1

Basic information such as patient age, gender, and fracture site will be extracted from the hospital medical record system. We will record the basic information of the included participants, which include age, gender, location of facture, smoking, frequency and mode of exercise, accompanied disease, long-term medication (name of medication, dose, and frequency of administration), and other conditions that related to bone fracture.

#### Measurement of bone metabolic markers

2.4.2

Serum β-CTX, OC, PINP, 25-OH-VitD_3_, and S-CTX were measured by using Elisa method (Shanghai Zhuocai Biological Technology Co., Ltd., China). Urinary calcium and creatinine were measured with automatic biochemical analyzer (Hitachi 7600, Japan).

#### Measurement of serum H_2_S

2.4.3

We will use modified methylene blue method for measurement of H_2_S level.^[14]^ We will add Zn^2+^ to serum sample to deposit H_2_S, HS^−^, S^2−^, and plasma protein; NaOH will then be used to re-dissolve plasma protein. ZnS deposition was re-dissolved by the addition of N, N-dimethyl-p-phenylenediamine, and the remnant protein was deposited by trichloroacetic acid. After centrifugation, ferriammonium sulfate was added to the supernatant fluid to generate methylene blue, which was analyzed by spectrophotometer at 665 nm.

### Outcomes

2.5

Standard for fracture healing:

(1)No pain in the fracture part and no pain along the longitudinal axis.(2)Raise the limb without discomfort.(3)Use proper force to reverse the affected limb and no abnormal activity in the fracture.(4)The injured limb can meet the following requirements to lift 1 kg weight to 1 minute; The lower extremity can walk 3 minutes without holding on the ground, not less than 30 steps. Continuous observation of 2 weeks of fracture without deformation.(5)X-ray shows the fracture line blurred, with continuous callus through the fracture line.^[15,16]^ Fracture healing was defined as being up to the all above standards.

Fracture healing is judged by 2 experienced orthopedic physicians, which usually takes 4 to 8 months after reduction and fixation, and if not heal for more than 9 months, it is considered delayed or non-union.^[17]^

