#### Inclusion criteria

2.2.1

Patients with spinal or limb fracture will be recruited. Patients with fracture occurred within 3 weeks will be included, and the fracture should be confirmed by X-ray or CT. All patients (1000 patients) will be asked to provide written informed consent.

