#### Exclusion criteria

2.2.2

Patients with wound infection or serious injury requiring amputation will be excluded. Patients with a predicted survival time of less than 9 months because of other serious illness will also be excluded. Patients with pregnancy, psychological disturbance that affects outcome evaluation, or cognitive impairment will also be excluded.

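### A patient whose fracture site has been wholly replaced or removed is eligible but can never be classed as healed, so is counted as delayed or non-union whatever the serum H2S

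*Protocol article*

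**What the plan says.** **Eligibility (protocol article, 2.2.1 and 2.2.2).** "Patients with spinal or limb fracture will be recruited". The further conditions concern recency and imaging: "Patients with fracture occurred within 3 weeks will be included, and the fracture should be confirmed by X-ray or CT". The one exclusion that turns on how the injury is treated is in 2.2.2: "Patients with wound infection or serious injury requiring amputation will be excluded". The other exclusions concern short predicted survival, pregnancy, psychological disturbance and cognitive impairment. No criterion refers to the type of operation.

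**Healing (2.5).** Five standards are listed. The radiographic one is "X-ray shows the fracture line blurred, with continuous callus through the fracture line". They apply jointly: "Fracture healing was defined as being up to the all above standards". The default follows: "if not heal for more than 9 months, it is considered delayed or non-union". Two experienced orthopedic physicians make the judgement.

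**Use.** The Abstract compares serum parameters between patients healed within 9 months and those unhealed at 9 months. Section 2.6 tests the same contrast with the t or Mann-Whitney test and makes healing at 9 months the dependent variable of the logistic model. Section 2.1 lists time from surgery to healing as a secondary outcome.

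**The concern.** Some fractures are managed by replacing the joint or taking out the fractured part. Where that removes the whole fracture site, there is no line left to blur and no callus to cross it. Such a patient may function well and meet every clinical standard, yet still fails the fifth. The outcome is then fixed by the operation and carries no information about H2S and bone healing.

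Two consequences follow. First, the unhealed group mixes fractures that failed to unite with patients in whom there was nothing to unite, which pulls a true difference in H2S towards zero. Second, if replaced patients differ from the others in age, illness or medication, and H2S varies with these, the unadjusted tests may show a difference that has nothing to do with healing. For time to healing, these patients have no possible event.

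**Working it through.** **Step 1: follow the rules for one patient.** Take an eligible limb fracture treated by complete replacement of the fractured part.

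- 2.2.1: limb fracture, recent, confirmed on imaging. Admitted.
- 2.2.2: no amputation and no other listed reason. Not excluded.
- 2.5, fifth standard: no fracture line exists. Not met.
- 2.5, joint rule: one standard failed. Not healed.
- 2.5, default: still not healed after 9 months. Delayed or non-union.
- 2.6: counted as unhealed in the tests and the logistic model.

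The probability of being classed as healed is 0 at every level of H2S.

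**Step 2: possible size.** The article gives no figure to reproduce: the 1000 patients in 2.2.1 come with no effect size, event rate or power. What follows illustrates assumptions.

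Inputs:
- N = 1000 (2.2.1), all taken as fracture patients. The shares below do not depend on N; the power figures do.
- a = share with the site wholly replaced or removed: 1% to 10%, assumed.
- p = share unhealed among the rest: 5% to 10%, assumed.
- True standardised H2S difference 0.3, assumed. Two-sided 5% test, assumed, since 2.6 gives .05 without sidedness.
- Replaced patients have the same mean H2S as healed patients, assumed.

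Formulas: unhealed U = N·a + N·(1−a)·p; replaced share of the unhealed f = N·a / U; observed difference = 0.3 × (1−f).

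Example, a = 5% and p = 10%: U = 50 + 95 = 145; f = 50/145 = 34%; observed difference = 0.3 × 0.66 = 0.20.

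| a | p | U | f | Observed difference | Power, left out | Power, counted unhealed |
|---|---|---|---|---|---|---|
| 1% | 5% | 59.5 | 17% | 0.25 | 54% | 46% |
| 1% | 10% | 109 | 9% | 0.27 | 81% | 77% |
| 2% | 5% | 69 | 29% | 0.21 | 54% | 40% |
| 2% | 10% | 118 | 17% | 0.25 | 80% | 72% |
| 5% | 5% | 97.5 | 51% | 0.15 | 52% | 28% |
| 5% | 10% | 145 | 34% | 0.20 | 79% | 59% |
| 10% | 5% | 145 | 69% | 0.09 | 50% | 18% |
| 10% | 10% | 190 | 53% | 0.14 | 77% | 42% |

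**Step 3: more of the rest unhealed.** The class covers delayed union as well as non-union, and all five standards must be met, so p may exceed 10%.
- a = 5%: p = 20% gives 50/(50 + 190) = 21%; p = 30% gives 50/(50 + 285) = 15%.
- a = 2%: p = 20% gives 20/(20 + 196) = 9%; p = 30% gives 20/(20 + 294) = 6%.

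**Step 4: confounding in the unadjusted tests.** Suppose H2S has no effect on healing, but replaced patients differ from the others by d SD. The spurious difference is d × f, with SE = √(1/U + 1/(N−U)).
- a = 5%, p = 10%: SE = 0.090. For d = 0.3 the difference is 0.10 and the test rejects in 21% of studies; for d = 0.5 it is 0.17 and 48%; for d = 0.1 rejection is 7%.
- a = 2%, p = 10%: SE = √(1/118 + 1/882) = 0.098. Rejection is 8% for d = 0.3 and 14% for d = 0.5.

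No value of d is supported by the article.

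**The case against.** **The article never mentions joint replacement or excision, and its only treatment wording points to fixed fractures.** Section 2.5 says of healing: "which usually takes 4 to 8 months after reduction and fixation, and if not heal for more than 9 months, it is considered delayed or" non-union. This does suggest that the authors had reduced and fixed fractures in mind. But it is a remark on usual healing time. It limits neither enrolment nor the patients to whom the classification applies. What stands is that the number of such patients is unknown.

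**A condensed article may leave evaluability to the full protocol or SAP.** A missing detail would not be a finding. Here the article states its eligibility criteria, a joint definition and a default class, and together these put a patient in the wrong group.

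**Two experienced physicians would not record a prosthesis as non-union.** Perhaps not, but the text gives them no other class, and handling such cases ad hoc would leave group membership unplanned.

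**The logistic model adjusts.** Section 2.6 plans age, gender, baseline characteristics and other parameters as covariates, and 2.4.1 collects accompanying disease and long-term medication. This partly answers the confounding argument, which therefore bears mainly on the unadjusted tests. It does not cure dilution.

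**Stronger readings that a reader might infer, and that the documents do not support:**
- That false-positive rates of 21% to 48% are to be expected. These belong to one assumed combination and an unsupported difference in H2S; another plausible combination gives 8% to 14%.
- That every excision is affected. After partial excision a remaining fracture line can still be assessed.
- That the amputation exclusion shows the plan already applying this principle. Section 2.2.2 gives no reason for it.

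**Conclusion.** The concern holds as a matter of logic. Open eligibility, the all-standards rule and the 9-month default together make healed status impossible for a patient with no remaining fracture site, and such a patient is analysed as unhealed. The main effect is dilution; confounding of the unadjusted tests is possible.

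The size cannot be established from the article. Under the assumed 1% to 10% replaced and 5% to 10% unhealed in the rest, these patients are about 9% to 69% of the unhealed group, and an assumed 0.3 SD difference shrinks to between 0.27 and 0.09. At 2% replaced and 20% to 30% unhealed in the rest, the share is only 9% to 6%. The dilution figures also assume that replaced patients resemble healed patients in H2S. It would be wrong to conclude that the healed-versus-unhealed comparison is known to be seriously biased: the effect could be small. The correction is worth making because it is cheap and removes outcomes that cannot depend on H2S.

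**What to change.** State in 2.5 and 2.6 that patients with no remaining fracture site that can unite, because of joint replacement or complete removal of the fractured part, are not assessable for union. Leave them out of the healed-versus-unhealed comparison, the logistic model and time to healing. Keep them in the description of baseline serum H2S in fracture patients. Patients with a remaining fracture line after partial excision stay in the healing analyses. Identify the group by a flag taken from the hospital medical record, which 2.4.1 already uses, and report how many patients it removes.

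The cost is a sentence or two on the analysis population, one extra data item, and a slightly smaller healing analysis set. The patients lost cannot inform the healing question, and no one's treatment or follow-up changes.

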**Methods::**

This is a single-center, prospective cohort study. Patients with spinal or limb fracture will be recruited. Patient's serum and urine will be collected at baseline for examination (serum H_2_S, β-CTX, OC, PINP, 25-OH-VitD_3_, S-CTX, urinary calcium, and urinary creatinine). All patients will be followed-up for 24 months in outpatients settings, the image of X-ray or CT will be reviewed and fracture healing will be judged by 2 experienced orthopedic physicians. The difference in serum parameters especially H_2_S will be compared between patients with fracture healed within 9 months and those with fracture unhealed at 9 months.

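### The all-standards healing definition is partly worded for limbs and cannot be applied as written to the eligible spinal fractures, so their 9-month status is undefined

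*Protocol article*

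**What the plan says.** **Eligibility.** Section 2.2.1 (Inclusion criteria) states: "Patients with spinal or limb fracture will be recruited". The Methods part of the abstract admits the same two sites. Neither place gives a target split between them.

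**Definition of healing.** Section 2.5 (Outcomes) lists five numbered standards:

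1. "No pain in the fracture part and no pain along the longitudinal axis"
2. "Raise the limb without discomfort"
3. "Use proper force to reverse the affected limb and no abnormal activity in the fracture"
4. "The injured limb can meet the following requirements to lift 1 kg weight to 1 minute", followed by a walking test for the lower extremity and two weeks of observation without deformity
5. "X-ray shows the fracture line blurred, with continuous callus through the fracture line"

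The combination rule follows: "Fracture healing was defined as being up to the all above standards". Two experienced orthopedic physicians make the judgement. A fracture still unhealed beyond 9 months is counted as delayed or non-union.

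**Use of the definition.** The abstract compares serum parameters, H2S above all, between patients healed within 9 months and those unhealed at 9 months. Section 2.6 (Planned statistical analysis) makes healed status at 9 months the dependent variable of a logistic regression on H2S. Section 2.1 (Study design) also lists time from surgery to healing as a secondary outcome.

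**The concern.** A spinal fracture has no affected or injured limb, yet the rule demands every standard and makes no exception. The protocol therefore admits a group of patients for whom its own healing outcome cannot be scored as written.

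Serum H2S is nominally the primary outcome, but the scientific question, whether H2S is related to healing, is answered only through the healed/unhealed split. If that split partly reflects fracture site, any difference in H2S between spinal and limb patients that has nothing to do with healing will appear in the healed-versus-unhealed contrast. The t tests and Mann–Whitney tests in section 2.6 are unadjusted. The logistic model adjusts for baseline characteristics in general terms and does not name fracture site.

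**Working it through.** **Step 1: set each standard against a spinal fracture.**

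| Standard | Wording | Can it be applied to a spinal fracture? |
|---|---|---|
| 1 Pain | fracture part, longitudinal axis | Yes |
| 2 Raising | the limb | Limb-worded; a spinal patient may be able to do it, but it does not test the fracture |
| 3 Manipulation | the affected limb | No affected limb exists |
| 4 Function | the injured limb; the lower extremity | No injured limb exists; the tasks may be possible, but the text ties them to an injured limb |
| 5 X-ray | fracture line and callus | Not limb-worded |

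Standards 2–4 are worded for a limb, and at least 3 and the first part of 4 have no referent in a spinal patient.

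**Step 2: go through the possible scoring rules.** The document does not choose among them.

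- *Not applicable counts as not met.* This is the literal effect of requiring all standards. Every spinal patient is unhealed, and is delayed or non-union after 9 months, whatever the bone shows.
- *Not applicable is waived or treated as met.* The automatic failure disappears, but spinal patients face fewer effective standards than limb patients, so healing means something different by site.
- *Not assessable.* The outcome is missing for a whole eligible stratum.
- *Left to the two physicians.* The operative rule is unwritten and may vary between patients or assessors.

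Under each rule, the outcome or its availability depends on fracture site.

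**Step 3: illustrate the size under the first rule only.** The document gives no figure to reproduce. It states 1000 patients (section 2.2.1), taken here as the number of fracture patients. It gives neither the spinal share *s* nor the unhealed share *u* among limb fractures, so both are assumptions. A third assumption is that every spinal patient is scored unhealed.

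- Unhealed = 1000·s + 1000·(1 − s)·u
- Spinal share of the unhealed = s / [s + (1 − s)·u], which does not depend on the total

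| s | u = 5% | u = 10% |
|---|---|---|
| 10% | 100 + 45 = 145; 100/145 = 69% | 100 + 90 = 190; 100/190 = 53% |
| 20% | 200 + 40 = 240; 200/240 = 83% | 200 + 80 = 280; 200/280 = 71% |
| 30% | 300 + 35 = 335; 300/335 = 90% | 300 + 70 = 370; 300/370 = 81% |

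Under the second rule, this distortion is zero. The text is therefore compatible with anything from no distortion of this kind to an unhealed group that is mostly spinal.

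**Step 4: would adjustment for site repair it?** Site is recorded (section 2.4.1, Basic information) and could enter the model. Under the first rule, site would predict the outcome perfectly among spinal patients: its coefficient would have no finite estimate, and those patients would add no information on H2S. Adjustment helps only once the outcome has a meaning at each site.

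**The case against.** Nothing in section 2.5 says that a standard which does not apply counts as failed. A spinal patient can raise a limb, lift 1 kg and walk for 3 minutes. Standards 1 and 5 fit any site, and two experienced physicians make the judgement. The article is also condensed, so scoring instructions by site might sit in a fuller protocol or case report form.

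The first part of this stands. A reader might infer that spinal patients are unhealed by construction, or take 53–90% as an estimate of the bias. The document supports neither. The first holds only if not applicable is scored as not met; the second adds assumed spinal shares and non-union rates to that scoring.

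Two further inferences should not be drawn:

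- That an arm fracture must also pass the walking test. Standard 4 reads naturally as one task for the arm and another for the leg, and most patients with an arm fracture can walk in any case.
- That the imaging requirement contradicts the abstract, where "the image of X-ray or CT will be reviewed and fracture healing will be judged by 2 experienced orthopedic physicians". Reviewing CT images as well does not conflict with requiring an X-ray sign.

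The appeal to a fuller document does not remove the point. The article presents its definition and combination rule as complete, and these conflict with its own eligibility criterion. Physician judgement does not remove it either, because the rule being judged has no stated content for the spine.

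**Conclusion.** The point holds in this form: the healing definition cannot be applied as written to spinal fractures, so the 9-month status of an eligible stratum is undefined. On the literal reading it is unhealed; on any other it rests on an unstated standard. This status forms the comparison groups and the logistic outcome, so the H2S contrast can be confounded by fracture site. The defect itself is read directly from sections 2.2.1 and 2.5 and needs no assumption.

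The size of the distortion cannot be derived from the document; the figures in the working show only how far the literal scoring could reach. The ambiguity should nonetheless be resolved before analysis, because the outcome on which the study's question depends should not be left to a choice made after H2S results are known.

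**What to change.** Reconcile sections 2.2.1 and 2.5 before any H2S result is linked to healing status, in one of two ways:

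- State which standards apply to which fracture site and how an item that does not apply is scored. Which criteria suit the spine is for the investigators to decide and write down.
- Limit the healed/unhealed analysis to the sites the present definition covers, and say so.

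If spinal patients stay in, report limb and spinal results separately, or name fracture site as a covariate in the section 2.6 model. The covariate supplements a definition that works at each site and does not replace one. Use the same definition for the time-to-healing outcome in section 2.1.

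The cost is revised outcome wording, a change to case report form scoring and a little extra analysis. Separate results by site rest on smaller numbers and will be less precise; limiting the analysis to covered sites gives up the spinal patients for this comparison.

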### Planned statistical analysis

2.6

The analysis will be conducted by Statistical Package for the Social Sciences (SPSS) Statistics software, version 19.0 (IBM Corporation, Armonk, NY). Continuous data will be presented as the mean ± standard deviation (

), while categorical data will be presented as raw numbers and frequencies. Kolmogorov-Smirnov and Shapiro-Wilk tests will be used to test whether data distribution is normal. Data with normal distribution will be analyzed by Student *t* test. Non-parametric tests Mann–Whitney *U* test will be used to assess the difference between patients with healed fracture and those without when data distribution is skewed. Logistic regression model will be developed with whether fracture is healed at 9 months as dependent variable, with level of H_2_S as independent variable, and with age, gender, baseline characteristics, and other parameters as covariates. *P* < .05 is considered statistical significance.

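### The planned Student t test misses its 5% level if the healed and unhealed groups differ in both size and spread; fix one Welch test in advance

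*Protocol article*

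**What the plan says.** Section 2.6 (Planned statistical analysis) sets a two-stage rule. First, "Kolmogorov-Smirnov and Shapiro-Wilk tests will be used to test whether data distribution is normal". Then "Data with normal distribution will be analyzed by Student"'s t test, while Mann-Whitney "will be used to assess the difference between patients with healed fracture and those without when data distribution is skewed". The threshold is P "< .05 is considered statistical significance". No unequal-variance form of the t test is named.

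The same section plans a logistic regression of healing at 9 months on H2S with covariates. That model does not pass through the normality tests.

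On group sizes, section 2.2.1 gives only the total: "All patients (1000 patients) will be asked to provide written informed consent". Section 2.5 says of healing, "which usually takes 4 to 8 months after reduction and fixation", and "if not heal for more than 9 months, it is considered delayed or non-union". The article gives no expected share unhealed and no SD for H2S or any marker.

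**The concern.** The abstract singles out the comparison of serum parameters, H2S above all, between patients healed within 9 months and those unhealed at 9 months. Section 2.1 makes serum H2S the primary outcome. The test stated for that comparison therefore matters.

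Student's t test estimates one common variance, weighted by group size. In a sample dominated by healed patients, that estimate is close to the healed variance. The uncertainty of the difference, however, comes mostly from the small unhealed group. If unhealed patients vary more, the standard error is too small and false positives rise. If they vary less, it is too large and the test loses power.

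The normality step adds a separate problem. A normality test's verdict depends on sample size as well as on shape, and a t test and a rank test answer different questions. One marker may be reported as a mean difference and the next as a rank shift, with the data deciding which.

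**Working it through.** **Inputs.** Total N = 1000 (section 2.2.1) and significance level 0.05 (section 2.6; two-sided assumed). Assumed, because the article does not give them: an unhealed share of 5%, 10%, 20% or 30%, with 50% as reference, and an unhealed-to-healed SD ratio r from 2/3 to 2.

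**Formula.** Let n1 be healed, n2 unhealed, and the healed SD 1.

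- Pooled variance: s² = [(n1 − 1) + (n2 − 1)r²] / (n1 + n2 − 2)
- Variance the t test uses: A = s²(1/n1 + 1/n2)
- True variance of the mean difference: B = 1/n1 + r²/n2
- Large-sample type I error: 2[1 − Φ(1.96 × √(A/B))]

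**The plan's own figure.** With r = 1, A = B, so the error is 5.0% at every split. The stated level is reproduced when spreads are equal.

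**One case in full (950:50, r = 1.5).** s² = (949 + 49 × 2.25)/998 = 1.0614. A = 1.0614 × 0.02105 = 0.02234. B = 0.00105 + 0.04500 = 0.04605. √(A/B) = 0.697, and 1.96 × 0.697 = 1.365, which gives 17.2%.

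**Type I error of Student's t over the assumed range:**

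| Unhealed share | r = 2/3 | r = 1 | r = 1.25 | r = 1.5 | r = 2 |
|---|---|---|---|---|---|
| 5% | 0.5% | 5.0% | 10.9% | 17.2% | 28.5% |
| 10% | 0.7% | 5.0% | 10.1% | 15.4% | 24.6% |
| 20% | 1.3% | 5.0% | 8.6% | 12.1% | 17.9% |
| 30% | 2.2% | 5.0% | 7.3% | 9.3% | 12.5% |
| 50% | 5.0% | 5.0% | 5.0% | 5.0% | 5.0% |

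**The two-stage rule as planned.** This was simulated with normal data, 2000 replicates per case, and Shapiro-Wilk at 0.05 in each group. Kolmogorov-Smirnov was not simulated.

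| Split | r = 1 | r = 1.5 | r = 2 | r = 0.5 |
|---|---|---|---|---|
| 950:50 | 5.2% | 17.9% | 26.5% | 0.2% |
| 900:100 | 4.5% | 14.5% | 23.5% | 0.4% |
| 800:200 | 5.3% | 11.2% | 17.6% | 0.9% |

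Identical lognormal distributions in both groups (950:50 and 900:100) gave 4.4% to 5.2%. Welch's test gave 4.0% to 5.8% across the normal-data cases.

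**Is the pre-test the cause?** No. At 950:50 and r = 2, always using Student's t gives 27.8%, against 26.5% with the pre-test. Testing normality on the pooled sample gives 15.3%, because that test then usually sends the data to Mann-Whitney.

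**Mann-Whitney under unequal spread.** With normal data and r = 1.5 to 2 it rejects 8.5% to 13.4% of the time. With equal-median lognormal data and a more variable unhealed group it rejects about 10% to 13%.

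**Sample size and the choice of test.** For a near-normal variable (gamma with shape 50, skewness 0.28), Shapiro-Wilk rejects 88% of the time at n = 920 and 15% at n = 80.

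**Cost of Welch when variances are equal.** Take an effect giving about 80% power with Student's t (noncentrality 2.8) and use Welch's approximate degrees of freedom. Power falls from 79.9% to 78.5% at 950:50, to 79.3% at 900:100 and to 79.8% at 700:300.

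**The case against.** **The 5% level may well hold.** A reader might infer that pre-testing with very unequal groups breaks the 5% level by itself. The documents do not support that. With equal spread the two-stage rule stays at about 5%, and the article gives neither group sizes nor SDs. If H2S had no relation at all to healing, its distribution would be the same in both groups and the level would hold. This stands, and it is why the point is conditional. But a t test result is read as a statement about means, and nothing in the plan makes equal spread a safe assumption.

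**Skewed markers never reach the t test.** This is largely true. In the simulations with clear lognormal skew, the rule always went to Mann-Whitney. Even for the near-normal variable above, a per-group rule at 920:80 would reach Student's t only about 0.12 × 0.85 = 10% of the time. The t-test errors therefore apply to markers that pass as normal. The Mann-Whitney branch is less affected, but it does not hold 5% under unequal spread either.

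**This is detail for an analysis plan.** Which normality test governs, and whether it is applied per group or pooled, can fairly be left to such a plan and is not raised here. The choice between Student's t and Mann-Whitney is different, because section 2.6 states it.

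**The logistic regression covers the question.** It bypasses the pre-test and is unaffected. The planned group comparisons of H2S and the markers are still exposed.

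**Conclusion.** The point holds conditionally. If the 9-month groups differ in both size and spread, the planned Student's t test misses 5% materially. The direction depends on which group varies more: with 5% to 30% unhealed, the error is about 17% to 9% at an SD ratio of 1.5, and about 0.5% to 2% at two thirds. A ratio of 1.25 already gives about 11% to 7%. With equal SDs, or with equal group sizes, the level is about 5%.

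That the unhealed are a minority is an inference from the healing times in section 2.5. The shares and SD ratios are assumptions. The failure comes from the pooled variance; the separate fault of the pre-test is that it leaves the estimand to the data. This is a cheap improvement to a stated method, not proof that the reported P values will be wrong.

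**What to change.** In section 2.6, remove the normality pre-tests. Pre-specify Welch's unequal-variance t test with a 95% CI for H2S and every marker, on one scale fixed in advance for all of them. The log scale, reported as a ratio of geometric means, is one option. The scale should not be chosen marker by marker according to observed skewness, because that would bring back the data-driven choice. Keep Mann-Whitney as a sensitivity analysis only, and leave the logistic regression as it is.

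The cost is about two sentences of text. If variances are equal, the power loss is about 1 percentage point or less: 1.4 points at 950:50, 0.6 at 900:100 and under 0.1 at 700:300, in the case worked above.
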